#### 7.1.6.2. Incomplete Dates

If the onset date of the AE is incomplete and the AE stop date is not prior to the first dosing date of study drug, then the month and year (or year alone if month is not recorded) of onset determine whether an AE is treatment emergent.

An AE with completely missing onset and stop dates, or with the onset date missing and a stop date later than the date of the first dose of study drug, will be considered to be treatment emergent. In addition, an AE with the onset date missing and incomplete stop date with the same or later month and year (or year alone if month is not recorded) as the first dosing date of study drug will be considered treatment emergent.

#### 7.1.6.3. Summaries of Adverse Events and Deaths

Treatment-emergent AEs will be summarized based on the Safety Analysis Set.

The number and percentage of subjects who experienced at least 1 TEAE will be provided and summarized by SOC, PT, and treatment group as follows:

- All TEAEs
- TEAEs of Grade 3 or higher
- TEAEs of Grade 2 or higher
- All TEAEs by severity grade
- All TE treatment-related AEs
- TE treatment-related AEs of Grade 3 or higher (by maximum severity)
- TE treatment-related AEs of Grade 2 or higher
- All TE treatment-related AEs by severity grade
- All TEAEs related to study procedures
- All TESAEs

- All TE treatment-related SAEs
- All TEAEs leading to premature discontinuation of study drug
- All TEAEs leading to premature discontinuation of study

A brief, high-level summary of AEs described above will be provided by treatment group and by the number and percentage of subjects who experienced the above AEs. All deaths observed in the study will also be included in this summary.

Multiple events will be counted only once per subject per treatment in each summary. Adverse events will be summarized and listed first in alphabetic order of SOC and then by PT in descending order of total frequency within each SOC. For summaries by severity grade, the most severe grade will be used for those AEs that occurred more than once in an individual subject per treatment during the study.

In addition, data listings will be provided for the following:

- All AEs, indicating whether the event is treatment emergent
- All AEs of Grade 3 or higher
- All AEs of Grade 2 or higher
- SAEs
- Deaths
- AEs leading to premature discontinuation of study drug
- AEs leading to discontinuation of study

## **7.2. Laboratory Evaluations**

Laboratory data collected during the study will be analyzed and summarized using both quantitative and qualitative methods. Summaries of laboratory data will be provided for the Safety Analysis Set and will include data collected up to the last dose of study drug plus 30 days for subjects who have permanently discontinued study drug. The analysis will be based on values reported in conventional units. When values are BLQ, they will be listed as such, and the imputed value will be used for the purpose of calculating summary statistics. Hemolyzed test results will not be included in the analysis, but they will be listed in by-subject laboratory listings.

A by-subject listing for laboratory test results will be provided by subject ID number and visit in chronological order for hematology, serum chemistry, lipids, coagulation, and urinalysis

separately. As appropriate, abnormal values will be flagged in data listings per Common Terminology Criteria for Adverse Events (CTCAE) v5.0 criteria.

No formal statistical testing is planned.

### **7.2.1. Summaries of Numeric Laboratory Results**

Descriptive statistics will be provided by treatment group for each laboratory test specified in the study protocol as follows:

- Predose values
- Values at each postdose visit
- Change from predose at each postdose visit

Predose and postdose values will be defined as described in Section 3.7.1. Change from predose to a postdose visit will be defined as the visit value minus the predose value. Laboratory test results collected at unscheduled visits will be included for the predose and postdose maximum and minimum value selection. The mean, median, Q1, Q3, minimum, and maximum values will be displayed to the reported number of digits; SD values will be displayed to the reported number of digits plus 1.

In the case of multiple values in an analysis window, data will be selected for analysis as described in Section 3.4.

### **7.2.2. Graded Laboratory Values**

As appropriate, CTCAE v5.0 will be used to assign toxicity grades to laboratory results for analysis. Treatment-Emergent Laboratory Abnormalities

Treatment-emergent laboratory abnormalities are defined as values that increase at least 1 toxicity grade from predose assessment associated with a treatment group and occurring after the first dose of that treatment group and on or before the date of the last dose of that treatment group plus 30 days or before the first dose of the following treatment group (if applicable), whichever occurs earlier. If the relevant predose laboratory value is missing, any abnormality of at least Grade 1 observed within the time frame specified above will be considered treatment emergent.

#### **7.2.2.1. Summaries of Laboratory Abnormalities**

Laboratory data that are categorical will be summarized using the number and percentage of subjects in the study with the given response at predose and each scheduled postdose visit.

The following summaries (number and percentage of subjects) for treatment-emergent laboratory abnormalities will be provided by lab test and treatment group; subjects will be categorized

according to the most severe postdose abnormality grade for a given lab test within a treatment group:

- Graded laboratory abnormalities
- Grade 3 or 4 laboratory abnormalities

For all summaries of laboratory abnormalities, the denominator is the number of subjects with nonmissing postdose values up to 30 days after last dosing date.

A by-subject listing of treatment-emergent Grade 3 or 4 laboratory abnormalities will be provided by subject ID number and visit in chronological order. This listing will include all test results that were collected throughout the study for the lab test of interest, with all applicable severity grades displayed.

### **7.2.3. Vital Signs**

Descriptive statistics will be provided by treatment group, including predose assessment on Day -1 (Baseline) and change from baseline at each postdose visit. Change from predose to postdose visit will be defined as the postdose value minus the predose value. Vital signs to be described include respiratory rate, heart rate, systolic blood pressure, diastolic blood pressure, and body temperature. In event of multiple values in an analysis window, data will be selected for analysis as described in Section 3.4. No formal statistical testing is planned. A by-subject listing of vital signs will be provided by subject ID number and visit in chronological order.

### **7.2.4. 12-lead Electrocardiograms**

ECG findings (Normal, Abnormal-not clinically significant, Abnormal-clinically significant) will be summarized by cohorts and study interventions. ECG parameters include ventricular rate, PR interval, QRS interval, QT interval, RR interval, and Summary statistics of measurement values and each change from baseline in ECG parameters will be calculated by cohorts and study interventions for each time point. The time points are shown in the tables under Section 13.

## **8. PHARMACOKINETIC ANALYSIS**

### **8.1.1. Data Handling**

All PK analyses will use the PK Analysis Set. Plasma concentrations and plasma PK parameters will be listed and summarized for TLC-2716 and its metabolites (TLC-6665, TLC-7255), as applicable using descriptive statistics by treatment and PK Day (as applicable) for each cohort. Plasma concentration versus time curves will also be presented.

Plasma concentrations that are below the limit of quantification (BLQ) will be treated as zero for calculation of descriptive statistics. When all concentrations are BLQ for a timepoint, the mean BLQ concentrations will be presented as BLQ, and the SD and CV will be reported as not applicable.

For PK parameter calculation, BLQ values prior to a quantifiable concentration will be treated as zero. BLQ values between 2 quantifiable concentrations, or in the terminal phase will be set as missing. If consecutive BLQ concentrations in the terminal phase are followed by quantifiable concentrations, those concentrations after consecutive BLQ concentrations will be treated as missing.

No missing data imputation will be performed.

Missing concentrations will be treated as missing from the descriptive statistics and PK parameter calculations.

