### 1.2.3. Nonclinical Pharmacokinetics (PK)

Absorption, distribution, metabolism, and elimination of TLC-2716, as well as the potential for drug-drug interactions, were assessed *in vitro* and *in vivo* in preclinical models. The pharmacokinetic (PK) profile indicates limited systemic exposure, with undetectable plasma levels 2-4 hours after dosing, and high levels in the liver consistent with rapid transporter-mediated uptake into hepatocytes.

TLC-2716 is a lipophilic, small molecule, LXR inverse agonist with a high binding affinity to plasma proteins (> 99%) in humans, mice, rats, dogs, and monkeys. Following intestinal absorption into the portal vein, TLC-2716 is highly extracted by the liver (92% hepatic extraction ratio in rats). Consistent with high liver loading, systemic exposure of TLC-2716 was generally low following oral administration in multiple species. In rodents, TLC-2716 was predominantly distributed to the liver and intestine; brain distribution data suggest that little or no TLC-2716-derived compounds cross the blood-brain barrier. *In vitro*, TLC-2716 was stable in primary hepatocytes from human, mouse, and dog. Together with the metabolites observed in

livers from preclinical species *in vivo*, the biotransformation pathway of TLC-2716 appears to involve oxidation, deamination, desulfation, glucuronidation, and taurine conjugation.

In *in vitro* studies, TLC-2716 was not a substrate of CYP1A2, CYP2B6, CYP2C8, CYP2C9, CYP2C19, CYP2D6, or CYP3A5, however, it was a modest substrate of CYP3A4 suggesting that co-administration of CYP3A4 inhibitors or inducers may affect the exposure of TLC-2716. TLC-2716 did not inhibit CYP1A2, CYP2C19, or CYP2D6, but demonstrated weak to modest inhibition of CYP2B6, CYP2C8, CYP2C9, and CYP3A4. In primary human hepatocytes, TLC-2716 induced CYP2B6 and CYP3A4 (> 2-fold relative to control), and therefore, may alter the exposures of co-administered substrates of these CYP enzymes *in vivo*. Finally, inhibition of P-gp, BCRP, OATP1B1, and OATP1B3 by TLC-2716 was observed *in vitro* at 10  $\mu$ M. While these findings suggest that TLC-2716 may alter the exposure of concomitant medications (and vice versa), the unique PK profile of TLC-2716, characterized by minimal systemic exposure and high protein binding, may reduce the potential for clinically relevant drug-drug interactions. Additional studies will be conducted to evaluate the clinical relevance of these findings.

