## 8.4. Data Handling Conventions

For summary statistics, PK concentration values below the limit of quantitation (BLQ) will be imputed as zero at pre-dose and one-half of the lower limit of quantitation (LLOQ) for post-dose time points.

Laboratory data that are continuous in nature but are less than the LLOQ or above the upper limit of quantitation (ULOQ) will be imputed to the value of the lower or upper limit minus or plus one significant digit, respectively (e.g., if the result of a continuous laboratory test is < 20, a value of 19 will be assigned; if the result of a continuous laboratory test is < 20.0, a value of 19.9 will be assigned).

Missing data can have an impact upon the interpretation of the trial data. As this study is of short duration, it is anticipated that missing data will be minimal. In general, values for missing data will not be imputed. However, a missing pretreatment laboratory result would be treated as normal (i.e., no toxicity grade) for the laboratory abnormality summary.

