##### **3.3.1. Data Handling Conventions and Transformations**

In general, age (in years) on the date of the first dose of study drug will be used for analyses and presentation in listings. If an enrolled subject was not dosed with any study drug, the randomization date will be used instead of the first dosing date of study drug. If only the birth year is collected on the CRF, “01 July” will be used for the unknown day of birth and month for the purpose of age calculation. If only birth year and month are collected, “01” will be used for the unknown day of birth.

Non-PK data that are continuous in nature but are less than the lower limit of quantitation (LOQ) or above the upper LOQ will be imputed as follows:

- A value that is 1 unit less than the lower LOQ will be used to calculate descriptive statistics if the datum is reported in the form of “< x” (where x is considered the lower LOQ). For example, if the values are reported as < 50 and < 5.0, values of 49 and 4.9, respectively, will be used to calculate summary statistics. An exception to this rule is any

value reported as  $< 1$  or  $< 0.1$ , etc. For values reported as  $< 1$  or  $< 0.1$ , a value of 0.9 or 0.09, respectively, will be used to calculate summary statistics.

- A value that is 1 unit above the upper LOQ will be used to calculate descriptive statistics if the datum is reported in the form of “ $> x$ ” (where  $x$  is considered the upper LOQ). Values with decimal points will follow the same logic as the bullet point above.
- The LOQ will be used to calculate descriptive statistics if the datum is reported in the form of “ $\leq x$ ” or “ $\geq x$ ” (where  $x$  is considered the lower or upper LOQ respectively).

If methods based on the assumption that the data are normally distributed are not adequate, analyses may be performed on transformed data or nonparametric analysis methods may be used, as appropriate.

Natural logarithmic transformation will be used for analyzing concentrations and PK parameters. Concentration values that are below the limit of quantitation (BLQ) will be presented as “BLQ” in the concentration data listing. Values that are BLQ will be treated as 0 at predose time points, and one-half the value of the LOQ at postdose time points for summary purposes.

The following conventions will be used for the presentation of summary and order statistics:

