- If at least 1 subject has a concentration value of BLQ for the time point, the minimum value will be displayed as “BLQ.”
- If more than 25% of the subjects have a concentration data value of BLQ for a given time point, the minimum and Q1 values will be displayed as “BLQ.”
- If more than 50% of the subjects have a concentration data value of BLQ for a given time point, the minimum, Q1, and median values will be displayed as “BLQ.”
- If more than 75% of the subjects have a concentration data value of BLQ for a given time point, the minimum, Q1, median, and Q3 values will be displayed as “BLQ.”
- If all subjects have concentration data values of BLQ for a given time point, all order statistics (minimum, Q1, median, Q3, and maximum) and summary statistics will be displayed as “BLQ.”

PK parameters that are BLQ will be imputed as one-half LOQ before log transformation or statistical model fitting.

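### SAP 8.1.1 and SAP 3.3.1 give different values for post-dose BLQ concentrations in the same PK summaries, and 3.3.1 allows half the LOQ to stand in for an AUC

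*Combined protocol and SAP*

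**What the plan says.** **Concentration summaries.** SAP 8.1.1 sets BLQ values to zero at every time point: "Plasma concentrations that are below the limit of quantification (BLQ) will be treated as zero for calculation of descriptive statistics". SAP 3.3.1 separates the times, with BLQ values "treated as 0 at predose time points, and one-half the value of the LOQ at postdose time points for summary purposes". Protocol 8.4 agrees with 3.3.1: for summary statistics, BLQ concentrations "will be imputed as zero at pre-dose and one-half of the lower limit of quantitation (LLOQ) for post-dose time points".

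**Display.** SAP 3.3.1 reads "If at least 1 subject has a concentration value of BLQ for the time point, the minimum value will be displayed as" BLQ, and it extends this to Q1, the median and Q3 once more than 25%, 50% and 75% of values are BLQ. SAP 8.1.1 changes the display only when every value at a time point is BLQ. The mean is then shown as BLQ, and the SD and CV as not applicable.

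**Parameter calculation.** SAP 8.1.1 has its own rule for the noncompartmental analysis: "For PK parameter calculation, BLQ values prior to a quantifiable concentration will be treated as zero". BLQ values that are embedded or terminal are set to missing. No other section contradicts this.

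**Parameter values.** SAP 3.3.1 adds: "PK parameters that are BLQ will be imputed as one-half LOQ before log transformation or statistical model fitting". It makes no exception for AUC.

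**The concern.** PK characterisation is a primary objective, and BLQ values may well be frequent. Protocol 1.2.3 reports "undetectable plasma levels 2-4 hours after dosing" in preclinical models, while post-dose sampling in this study runs to 72 hours and starts at 0.5 mg. Two questions follow.

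1. Which value goes into the concentration tables and mean plots? A programmer cannot satisfy both SAP sections, and 8.1.1 departs from the protocol without saying so. If this stays open until unblinded concentrations are in hand, the choice is made after seeing the data.
2. What happens to a subject whose whole profile is BLQ? Under 3.3.1 that subject might enter the log-scale power model of SAP 8.1.4.1 with LOQ/2 as the AUC. An LOQ is a concentration and an AUC is concentration × time, so the number has no meaning on that scale. The subjects most likely to be affected are at the lowest dose, which has the most leverage on the slope.

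**Working it through.** The documents state no result that depends on the BLQ rule and give no LOQ, so there is no figure to reproduce.

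**1. Gap in a time-point mean.** Inputs: 8 active subjects per cohort (SAP 1.2.1 and 1.2.2), and k of them BLQ at a post-dose time.

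Mean(LOQ/2 rule) − mean(zero rule) = (k/8) × LOQ/2

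- k = 1: 0.0625 × LOQ
- k = 4: 0.25 × LOQ
- k = 7: 0.4375 × LOQ

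Before dosing both rules give zero, so the conflict is post-dose only.

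**2. Spread.** Invented example with LOQ = 1, four BLQ values, and four measured values of 1.1, 1.3, 1.6 and 2.0:

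| Rule | Mean | SD | CV |
|---|---|---|---|
| Zero (8.1.1) | 0.75 | 0.842 | 112.2% |
| LOQ/2 (3.3.1) | 1.00 | 0.593 | 59.3% |

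Under the zero rule, mean − SD = 0.75 − 0.842 = −0.092. That cannot be drawn on the semi-logarithmic mean ± SD plot planned in SAP 8.1.2. The minimum would print as 0 under 8.1.1 and as BLQ under 3.3.1.

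**3. Does this conflict reach the slope?** No. The 3.3.1 concentration rule is limited to summaries and the 8.1.1 zero rule to descriptive statistics. Cmax and AUC come from the separate 8.1.1 calculation rule. The effect on the power-model slope is zero.

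**4. Units of the parameter rule.** Changing the time unit from hours to minutes multiplies every observed AUC by 60 but leaves LOQ/2 as it is. On the log scale the imputed points then move by ln 60 = 4.09 relative to the observed ones.

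**5. Scale.** Protocol Table 1 gives a monkey AUC of 51.08 to 74.09 ng.h/mL and a 672-fold dose margin at 0.5 mg. Assuming linear scaling, 51.08/672 = 0.076 and 74.09/672 = 0.110 ng.h/mL. At that level LOQ/2 could be as large as the AUC it replaces, so the direction of the error is not known.

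**6. Sensitivity of the slope to the parameter rule.** A simulation with a true slope of 1; doses of 0.5, 2, 6, 12 and 20 mg; 8 subjects per dose; and 2,000 runs. These further settings are assumptions: a one-compartment oral profile, between-subject CV of 40%, AUClast in hours under the 8.1.1 calculation rule, and an LOQ set as a multiple of the median Cmax at 0.5 mg. The table shows mean slopes.

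| LOQ multiple | All-BLQ at 0.5 mg | Cmax: excluded / LOQ/2 | AUClast: excluded / LOQ/2 |
|---|---|---|---|
| 0.5 | 4% | 0.991 / 1.006 | 1.129 / 1.149 |
| 1 | 49% | 0.940 / 1.045 | 1.197 / 1.314 |
| 1.5 | 84% | 0.940 / 1.035 | 1.182 / 1.298 |
| 3 | about 100% | 0.929 / 0.910 | 1.299 / 1.179 |

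For AUClast, imputing instead of excluding changes the slope by +0.020, +0.117, +0.116 and −0.120, so the sign reverses at the highest LOQ. At multiple 1, the 90% interval for the AUClast slope contains the true value in 28.8% of runs with exclusion and 0.6% with LOQ/2. Part of the excess over 1 is truncation at the last quantifiable sample, which occurs under either rule.

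**The case against.** The best defence concerns the parameter rule. A parameter that is BLQ most naturally means a concentration-type parameter such as Cmax. SAP 8.1.3 calculates parameters only where the data allow and runs AUClast to the last quantifiable concentration, so an all-BLQ profile has no AUClast. SAP 8.1.1 rules out imputing missing data, and the PK Analysis Set in SAP 2.3 requires enough data to calculate parameters reliably. An all-BLQ subject may therefore drop out before 3.3.1 applies. This stands as a plausible reading, but 3.3.1 does not say it. The PK Analysis Set in protocol 8.3.1.2 asks only for one non-missing concentration value. The outcome is therefore undecided, which is why the slope effect is only possible.

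It is also fair that the concentration tables are not the primary PK endpoints; the parameters in protocol 8.1.2 are.

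A reader might infer three stronger points that the documents do not support:

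- **A false rise at the last trough** (0 before the Day 14 dose, LOQ/2 at 24 hours after it). SAP 8.1.2 labels later pre-dose samples as predose, but SAP 3.4.1 counts any value after the first dose of that treatment as postdose, which gives LOQ/2 to both. The SAP specifies no trough-based steady-state analysis, and protocol 8.7 only permits one. The labels are ambiguous; the artefact is not established.
- **Zeros that cannot be logged.** SAP 3.3.1 mentions log transformation of concentrations, but the statistics in SAP 8.1.2 are arithmetic, so no planned summary is affected.
- **An imputed AUC 4 to 8 times too low, raising the slope by 0.17 to 0.26.** The leverage is right: the sum of squares of ln dose is 69.94, the weight of the 0.5 mg mean is −0.246, and 0.5 × ln 4 × 0.246 = 0.17, or 0.26 with ln 8. But the input is a subject sitting at the LOQ for 2 to 4 hours. That subject is not BLQ and would not be imputed.

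**Conclusion.** Two faults hold, and both should be corrected before the analysis.

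First, SAP 8.1.1 contradicts SAP 3.3.1 and protocol 8.4 on post-dose BLQ concentrations in the same tables and mean plots, and the display conventions conflict as well. The gap in a mean is p × LOQ/2 for BLQ fraction p. It would be tempting to say that the dose-proportionality result depends on this choice. It does not, because the parameters are calculated under a separate and consistent rule.

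Second, the LOQ/2 rule for BLQ parameters is dimensionally wrong if applied to AUC, and it sits against SAP 2.3, 8.1.1 and 8.1.3. It could bias the slope only if all-BLQ profiles occur and are imputed, not excluded. The preclinical statement about undetectable levels at 2 to 4 hours does not establish that, since sampling starts at 0.25 hours. With no LOQ in the documents, neither the size nor the direction of any bias can be fixed. The simulated slopes are illustrations under stated assumptions, not predictions.

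**What to change.** - In SAP 8.1.1, delete the zero rule for descriptive statistics and refer to the SAP 3.3.1 / protocol 8.4 rule and the 3.3.1 display conventions. State whether the Day 3, 7 and 14 pre-dose troughs count as predose or postdose for this purpose, and document any departure from protocol 8.4.
- Keep the 8.1.1 rule for parameter calculation as it is.
- In SAP 3.3.1, limit LOQ/2 imputation to concentration-type parameters (Cmax, Ctau).
- Report AUC as not calculable when the whole profile is BLQ, and give the number of such subjects at each dose.
- Show the power-model slope with and without the affected low-dose cohort. A left-censored model is an option, not a requirement.

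The cost is a few sentences in the SAP and a small programming change, with no effect on conduct or sample size.
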